### Outcomes

The primary outcomes of the study include (figure 2):

Feasibility, acceptability and appropriateness—assessed by proportion of WRA enrolled, proportion of screen-positive WRA (SP-WRA), determined by a cut-off score of 3 or greater,^16 17^ proportion of WRA attending mental health awareness and resilience-building group sessions conducted by LHWs, proportion of SP-WRA presenting to BHU facility for further assessment, proportion of SP-WRA diagnosed with mild-moderate anxiety and/or depression and receiving two counselling sessions by BHU staff at facility and proportion of WRA with severe depression and/or anxiety accepting referral to specialist.

**Figure 2 F2:**
[figure not shown]
Study design and outcomes. BHU, Basic Health Unit; LHS, Lady Health Supervisors; LHWs, Lady Health Workers; WRA, Women of Reproductive Age.

The secondary outcome includes:

Effectiveness of intervention on mental health—defined by the prevalence of anxiety and depression among WRA in the intervention arm when compared with the control arm.

### Formative phase

A qualitative formative study was conducted prior to the intervention phase to understand the dynamics influencing mental health and climate resilience in the target population. FGDs and IDIs were used to gather insights into community perceptions and assess the feasibility and relevance of the intervention from the perspective of various stakeholders (guides attached in online supplemental material). Verbal informed consent was acquired from all participants before data collection. This component assessed the feasibility and acceptability of implementing four key strategies: home-based mental health screening, referrals, group mental health awareness sessions and climate change-related resilience-building sessions, all facilitated by LHWs for WRA. Four IDIs were conducted with stakeholders including Disaster Management Officials and healthcare facility staff along with five FGDs with LHWs, Lady Health Supervisors (LHS), BHU facility doctors and community members.

The findings showed that many WRA did not understand the term ‘mental health’; hence, the intervention included sessions on mental health awareness to increase their knowledge about common mental health disorders such as depression and anxiety. Moreover, the stigma regarding mental health, for those who were aware, can be challenged through mental health and resilience-building sessions and counselling provided by healthcare facility staff at BHUs. WRA showed willingness for home-based mental health screenings and group sessions by LHWs, whom they perceived as trustworthy. Consequently, these interactions provided valuable insights into participants’ perceptions, existing knowledge of mental health and climate change, the preparedness of health facilities to handle referrals, and the capacity of LHWs to carry out screenings effectively which were incorporated into the intervention phase (table 1).

**Table 1 T1:** Key findings of formative study (qualitative component)

Flood challenges and impacts	Participants unanimously regarded the 2022 flash floods as an unmitigated disaster, wiping out communities that received no prior warnings to evacuate. Many participants also lamented the rehabilitation process, with the entire experience leaving them physically drained and mentally traumatised. Women faced severe menstrual hygiene challenges due to a lack of menstrual products and a lack of privacy, using makeshift materials like dupattas. Sexual violence was also reported in shelters, especially in tents where families lived in close quarters, with minimal security. Some girls were raped, and victims’ families chose to remain silent due to social stigmas. Pregnant women suffered significantly, with some experiencing miscarriages and stillbirths due to stress, lack of medical care, and unsafe living and delivery conditions during the floods. Limited access to healthcare during the floods left pregnant women vulnerable to severe complications, including infections and maternal death.
Understanding of mental health	Initially, WRA did not understand the term ‘mental health,’ responding with confusion and silence. The trauma of the floods led to long-lasting mental health issues, with survivors experiencing symptoms like palpitations, anxiety and flashbacks during subsequent rains. Women, especially those who lost loved ones or their homes, were deeply affected, with some reporting persistent feelings of sadness, fear and helplessness. While there was recognition from almost all participants about the need for mental health services, some community members were unable to properly identify symptoms and issues.
Intervention feasibility and challenges	Overall, the proposed intervention was wholeheartedly welcomed by all study participants. Women highlighted challenges such as familial interference and refusals over permission to travel to healthcare facilities primarily and financial constraints. The stigma surrounding mental health in these communities was also highlighted as a challenge, with some women afraid of being labelled crazy and ostracised by others. While some facility staff questioned LHWs’ capabilities, community members highly trusted them, especially for maintaining privacy in sensitive areas like family planning and mental health. LHWs were also valued for their support in family planning and vaccinations. Facility staff highlighted issues related to space, training and human resources in their facilities, hindering the delivery of mental health support services. They also felt that issues with the existing LHW referrals system and record-keeping can cause logistical issues, leading to issues with tracking and follow-ups for the patients. WRA showed willingness for home-based mental health screenings by LHWs and expressed strong interest in group counselling sessions led by trusted LHWs.

LHWs, Lady Health Workers; WRA, Women of Reproductive Age.

### Pre-intervention phase

#### Development of counselling manuals

Manuals were designed by the research team of mPareshan,^23 24^ a study involving an app-based counselling intervention for flood-affected communities in Sindh. The content of this curriculum was adapted using the WHO Mental Health Gap Action Program-Intervention Guide V2.0 (mhGAP-IG 2.0).^25^ Three manuals were developed for this study: Improving Mental Health Awareness and Literacy: A Manual for Facility-Based Staff in Primary Care Settings, Improving Mental Health Awareness: A Manual for Frontline Community Health Workers Pakistan, and Responding to Climate Change – Community Awareness, Resilience-Building & First Response to Floods: A Trainer’s Manual for Frontline Workers to Build Resilience for Climate Change*.*

#### Hiring and training

The team for screening and delivering the intervention will include LHWs, LHS and BHU facility staff. The project will provide training to 20 LHWs in the intervention study arm to conduct household visits and administer screening tools. 12 female Senior Research Assistants (SRAs) along with four male SRAs will be recruited to assist.

The selected LHWs and LHS in the intervention clusters will receive training by the research team on screening using GAD-2 and PHQ-2, referral and provision of mental health awareness and resilience-building sessions. All BHU facility doctors will acquire training on assessment using GAD-7 and PHQ-9 of incoming referrals classified as screen-positive cases by LHWs, selection and administration of the most appropriate treatment strategies for mild or moderate cases (including counselling or psychoeducation for mild and moderate cases), and management and process of referral of severe cases for specialised care. Pre-training and post-training assessment of knowledge will be conducted for LHWs and LHS and communication and counselling skills for BHU or rural health clinic (RHC) facility staff.

#### Baseline assessment

A quantitative baseline will be conducted in the pre-intervention phase which will include a structured household survey to measure demographic information and screen for anxiety (GAD-7) and depression (PHQ-9). This component will focus on evaluating the feasibility of using LHWs for the purpose of screening and providing community interventions to WRA. By collecting baseline data, participants’ perceptions about mental health support and prior history regarding experiences of surviving floods will be assessed. This baseline survey will be carried out in both intervention and control arms. Informed consent will be acquired from all participants.

### Intervention phase

The intervention phase details are described below (figures3  4).

**Figure 3 F3:**

Tentative participants and data collectors during intervention phase. BHU, Basic Health Unit; LHS, Lady Health Supervisors; LHWs, Lady Health Workers; WRA, Women of Reproductive Age.

**Figure 4 F4:**
[figure not shown]
Data collection during intervention phase. BHU, Basic Health Unit; GAD-2, two-item Generalized Anxiety Disorder; GAD-7, 7-item Generalized Anxiety Disorder; LHWs, Lady Health Workers; PHQ-2, two-item Patient Health Questionnaire; PHQ-9, 9-item Patient Health Questionnaire; SP-WRAs, Screen-Positive Women of Reproductive Age; UC, Union Councils; WRA, women of reproductive age.

#### Intervention: Arm 1

The four UCs will receive community intervention provided by LHWs, LHS and BHU facility staff.

##### Implementation

The intervention involves several key components:

Step 1: Community-based mental health screening and referral by LHWs.

Trained LHWs will screen WRA using validated mental health tools, GAD-2 and PHQ-2.

WRA scoring 3 or above on either tool will be classified as screen-positive for anxiety^16^ and/or depression.^17^A total of at least 2400 WRA will be screened across the intervention area, with each LHW responsible for approximately at least 120 WRA.SP-WRA will be issued standardised referral slips and directed to BHUs assigned to their respective UCs, where health facility-based doctors will conduct further screening using PHQ-9 and GAD-7 assessments.

Step 2: Awareness-raising and resilience-building group sessions by LHWs.

LHWs will conduct structured group sessions aimed at increasing mental health awareness, enhancing emotional resilience and fostering community support systems. These sessions will follow a standardised curriculum developed by the research team of mPareshan^23 24^ (Responding to Climate Change: Community Awareness, Resilience-Building and First Response to Floods, Appendix C).

All WRA, regardless of their screening outcome, will participate in resilience-building group sessions to strengthen individual and community preparedness for future climate-related challenges.LHWs will provide three monthly sessions with each WRA attending two sessions, each lasting approximately 2 hours.Group sizes for each session will range from 20 to 25 WRA, ensuring interactive and supportive environments.LHS will monitor these sessions using a structured checklist to ensure fidelity to content and delivery standards.

Step 3: Facility-based counselling and referral pathways for screen-positive (SP) WRA.

WRA referred to BHU facilities will receive more comprehensive mental health assessments using the full PHQ-9 and GAD-7 tools. These assessments will be conducted by trained BHU doctors.

WRA identified as experiencing mild to moderate symptoms of anxiety and/or mild to moderate symptoms of depression will be offered two individual counselling sessions, following the protocol outlined in Improving Mental Health Awareness and Literacy: A Manual for Facility-Based Staff in Primary Care Settings, Module 4. These sessions will be spaced bi-monthly, each lasting a minimum of 20 minutes, and scheduled according to patient and provider availability.WRA classified in the severe category of anxiety and/or moderate-severe to severe categories of depression will be urgently referred to mental health professionals at Civil Hospital Larkana for specialised care. The study team will provide one-time transportation support and necessary facilitation for these high-risk cases.

### Control: Arm 2

The control arm will include four Union Councils: Dhani Bux Bughio, Parya, Thalo and Sindhi Butera. These UCs will not receive any form of intervention other than standard routine care provided by LHWs.

### Compliance

Compliance will be maintained by record keeping through regular attendance data of mental health awareness and resilience-building group sessions conducted by LHWs, and referral information stored by health facility staff at BHUs. Geo-tagged pictures will be collected for all sessions to document attendance of WRA and LHWs. Findings will inform the feasibility, scalability and sustainability of integrating climate-adaptive mental health services within Pakistan’s primary healthcare system, particularly in vulnerable, disaster-prone communities.

### Quality assurance

LHS will monitor mental health and resilience-building group sessions conducted by LHWs using checklists to assess the quality of content relayed to WRA. BHU facility staff will be evaluated through consistent monitoring feedback forms collected from referred WRA after initial and follow-up visits. The study team will be involved in monitoring the group sessions and individual counselling sessions to maintain the quality of the intervention.

### Post-intervention phase

After the completion of resilience-building sessions in 4 months, an endline survey will be conducted across both intervention and control areas. The survey will include PHQ-9 and GAD-7 tools to assess changes in mental health status among WRA. In addition to the quantitative survey, qualitative data will be collected through FGDs and IDIs to gain insights into the barriers and facilitators of the intervention, as well as the broader community context.

The endline survey and summative study will serve to evaluate the impact of the intervention, focusing on shifts in mental health status among WRA, provide a comprehensive understanding of the intervention’s effectiveness and identify areas for improvement.

### Data collection

#### Monitoring, evaluation and cost assessment

Throughout the implementation period, detailed monitoring and cost-tracking will be conducted to assess the fidelity, reach and resource implications of the intervention (table 2). This includes data on:

**Table 2 T2:** Study activities during implementation period

Study months and study activities	1	2	3	4	5	6	7	8	9	10	11	12
Formative research including data collection tools and application development (qualitative & quantitative surveys)	X	X	X									
Development of intervention components (manuals for LHWs, LHS and BHU facility staff)			X	X								
Recruitment & training (survey teams, BHU facility staff, LHWs, LHS)					X							
Baseline survey (household structured survey of WRA in intervention and control arms)					X							
Component A: LHW ultra-brief screening & referral (PHQ-2, GAD-2)						X						
Component B: LHW-led group mental health awareness & resilience-building sessions						X	X	X	X			
Component C: BHU assessment of referred SP-WRA (PHQ-9, GAD-7+case management)						X	X	X	X			
Endline PHQ-9 & GAD-7 administration (all WRA in intervention & control UCs)										X		
Data analysis											X	
Report writing & dissemination												X

BHU, Basic Health Unit; GAD-2, 2-item Generalized Anxiety Disorder; GAD-7, 7-item Generalized Anxiety Disorder; LHS, Lady Health Supervisors; LHWs, Lady Health Workers; PHQ-2, two-item Patient Health Questionnaire; PHQ-9, 9-item Patient Health Questionnaire; SP-WRA, screen-positive women of reproductive age; UCs, Union Councils; WRA, women of reproductive age.

Screening coverage and referral completion.Group session attendance and quality.Counselling uptake and outcomes at BHU facilities.Overall resource utilisation and programmatic cost-efficiency.

Following the screening by LHWs and BHU facility staff, referrals will be tracked through the Data Management Unit (DMU) of Aga Khan University which will generate daily summary reports for quality check and, if required, send the reports to the field teams for rectification. All the data were encrypted, secured and fully anonymised.

#### Baseline and endline data collection

Participants will be assessed on baseline and endline levels involving data on sociodemographic factors, health-related information, household indicators, maternal health, trauma, impact of displacement and mental health, that is, depression and anxiety.

##### Demographic and socioeconomic indicators of households

Information regarding socioeconomic status, gender, level of education, marital status, number of children, occupation of the household head, water, sanitation and hygiene (WASH), household infrastructure material, and financial and economic assets will be recorded.

##### Maternal health, diseases and morbidity

Types of diseases, duration, maternal health and pregnancy-related information will be collected.

##### Displacement and trauma

Information will be collected regarding fear and trauma experienced by WRA after surviving flooding involving loss of loved ones, financial and economic assets, houses, and agricultural livelihoods.

##### Mental health screening (GAD-7 and PHQ-9)

Screening tools that will be used for assessing symptoms of depression and anxiety are the GAD-2,^16^ PHQ-2,^17^ GAD-7^18^ and PHQ-9.^19^ All tools are reliable and valid for screening purposes^16^,^19^ and were translated into Sindhi language by a minimum of two native Sindhi-speaking researchers.

### Patient and public involvement

Stakeholders from the Sindh Lady Workers Programme and the District Health Department, and community members were involved in the design of the trial, as mentioned in the formative phase. Their perceptions and opinions regarding mental health screening and referral, and resilience-building sessions were used in the formation of the intervention, which may subsequently benefit the community.

### Data analysis

#### Quantitative component

The data collected and stored on the server will be exported to Stata version 18 for analysis. Data will be cleaned, and errors will be rectified under the guidance of the study investigators. Descriptive statistics will be presented: mean and SD, or median with IQRs for continuous variables, depending on the data distribution, and frequency distributions for categorical variables. Feasibility, acceptability and appropriateness of the intervention were assessed through proportions with 95% CIs. For mental health outcomes, difference-in-difference (DID) analyses will be conducted through logistic regression analysis, assuming parallel trends i.e., intervention and control arms had parallel trends in the outcomes before the intervention was introduced. The model incorporates an interaction term for time and intervention effect. The coefficient of the interaction term serves as DID estimate. Further, to address potential confounding, the DID will be adjusted for imbalanced factors at baseline. In addition, the model will also include covariates that are known to affect the outcome such as age, education, marital status, parity, socioeconomic status and trauma. For missing data on variables, the plan will be not to impute but treat this as missing and perform complete case analysis. All analysis will be adjusted to account for the cluster randomised design.

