### Sample Size

The sample size was calculated based on an estimated anxiety prevalence of 25.6%. To detect a 20% relative difference in prevalence between study arms with 90% power and a 5% level of significance, estimated intracluster correlation coefficient (ICC) of 0.0033 and an anticipated attrition rate of 10%, a total of 20 clusters per arm with 105 women per cluster (ie, 2100 women per arm) will be required. The prevalence of anxiety is assumed to vary by ±5 percentage points between clusters. The coefficient of variation (CV) was estimated based on this range, and the ICC was then derived using the CV formula.^21 22^

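### As the plan reads, covariates enter the logistic DID as main effects, which do not address different trends driven by imbalanced factors; covariate-by-time terms would

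*Protocol article*

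**What the plan says.** Under Study site, eight Union Councils in one Taluka were chosen purposively. Four went to each arm according to their side of the Taluka Headquarters, and no randomisation is described. Table 2 shows one survey before the intervention (month 5) and one after it (month 10).

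Under Data analysis, Quantitative component, the mental health outcomes are analysed by a logistic DID with parallel trends assumed. "The model incorporates an interaction term for time and intervention effect", and the coefficient of that term is the estimate. The article then says that "to address potential confounding, the DID will be adjusted for imbalanced factors at baseline". It adds covariates known to affect the outcome, naming age, education, marital status, parity, socioeconomic status and trauma as examples. It mentions no covariate-by-time term and excludes none.

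On trauma, the Displacement and trauma section says "Information will be collected regarding fear and trauma experienced by WRA after surviving flooding", and the parent section on baseline and endline data collection places this domain at both waves. The analysis section does not say which wave's value enters the model.

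**The concern.** A DID removes any difference in level between arms that stays the same across waves. After geographic assignment, what remains is confounding of change: a factor that is distributed differently in the two arms and whose effect on anxiety or depression differs between baseline and endline. A main effect gives the factor the same effect at both waves, so it cannot represent this. The article nevertheless presents the adjustment as its answer to confounding.

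The mechanism is plausible from the article itself. Table 1 reports that survivors had anxiety and flashbacks during later rains. If study month 1 is January 2025, the surveys fall in May and October, either side of the calendar month (June) in which the 2022 flooding is reported. The effect of flood trauma could therefore differ between the two surveys, in a direction the article gives no means of knowing. With a single pre-intervention wave, trial data cannot check parallel trends.

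At stake is the effectiveness estimate, which could be reported as adjusted for confounding while keeping a trend difference that the measured covariates could have removed.

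**Working it through.** **Reference effect.** Inputs from Sample Size: "To detect a 20% relative difference in prevalence between study arms with 90% power and a 5% level of significance", prevalence 25.6%, ICC 0.0033, attrition 10%, 105 women per cluster. A two-sided test is assumed.
- Target prevalence: 0.8 × 25.6% = 20.48%.
- n per arm = [1.960·√(2 × 0.2304 × 0.7696) + 1.282·√(0.256 × 0.744 + 0.2048 × 0.7952)]² / 0.0512² = 1420.
- Design effect: 1 + 104 × 0.0033 = 1.343, giving 1907. Attrition gives 1907/0.9 = 2119 or 1907 × 1.1 = 2098. The plan's 2100 per arm is reproduced, and this point does not affect it.
- Planned odds ratio: (0.2048/0.7952)/(0.256/0.744) = 0.748, log −0.290.

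**What a covariate X contributes to the DID.** Let X have effect β at baseline and β + γ at endline. On the linear-predictor scale (exact for a linear model, approximate for a logistic one):
- Stable case mix, γ = 0: the contribution is β × (0 − 0) = 0. It cancels without adjustment.
- Stable case mix, γ ≠ 0: the contribution is γ × (mean X in intervention − mean X in control). A main effect leaves it in place; an X-by-time term removes it.
- Case mix changing between waves, γ = 0: the contribution is β × (change in mean X in intervention − change in control). A main effect does remove this.

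**Exact population fits, no intervention effect.** The covariate inputs are assumptions; the documents give none. In rows 1 to 4 the logit is −1.2 + 0.2X − 0.1·time + γ·X·time. In rows 5 to 8 it is −1.5 + 0.8X − 0.1·time + γ·X·time.

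| X, intervention v control | γ | exp(γ × gap) | Unadjusted OR | Main effect | With X-by-time |
|---|---|---|---|---|---|
| 60% v 40% | 0.5 | 1.105 | 1.103 | 1.104 | 1.000 |
| 60% v 40% | 0.7 | 1.150 | 1.146 | 1.148 | 1.000 |
| 65% v 35% | 0.7 | 1.234 | 1.227 | 1.230 | 1.000 |
| 40% v 60% | 0.7 | 0.869 | 0.873 | 0.871 | 1.000 |
| 40% v 30% | −0.3 | 0.970 | 0.969 | 0.968 | 1.000 |
| 50% v 30% | −0.5 | 0.905 | 0.903 | 0.901 | 1.000 |
| 60% v 30% | −0.7 | 0.811 | 0.811 | 0.809 | 1.000 |
| 50% v 30% | 0 | 1.000 | 1.000 | 1.000 | 1.000 |

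Main-effect adjustment moves the odds ratio by at most about 0.003. Hand check of row 2, unadjusted: prevalence goes from 25.40% to 32.65% in intervention and from 24.65% to 28.90% in control. The odds ratios are 1.424 and 1.243, and their ratio is 1.146.

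**Size against the planned effect (log scale, main-effect model).** Row 1: ln 1.104/0.290 = 0.34. Row 2: ln 1.148/0.290 = 0.48. Row 3: ln 1.230/0.290 = 0.71. Row 5: 0.11. Rows 1 to 3 would mask that share of a benefit; rows 4 to 7 would mimic one.

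**Counter-case.** X falls from 50% to 40% in intervention and stays at 30% in control, β = 0.8, γ = 0. The unadjusted odds ratio is 0.924 (approximation exp(0.8 × −0.10) = 0.923), and the main effect restores 1.000.

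**Rejection at nominal 5%.** 400 simulated null trials per scenario, 20 clusters × 105 women per arm, two waves, cluster-robust errors, X 50% v 30%. Unadjusted / main effect / with X-by-time:
- γ = −0.5: 17% / 18% / 6%
- γ = −1.0: 43% / 43% / 6%
- γ = 0: 3.5% / 3.5% / 4.5%

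**The case against.** The strongest reply is that the article is condensed and does not state the form of the adjustment. It names the interaction that defines the estimate and then says the model is adjusted; covariate-by-time terms may be intended. That is fair. Main effects only is the natural reading, not a stated rule. But the article does state what the adjustment is for, and on that reading it does not match the threat that remains in a DID.

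A reader might infer that the planned adjustment achieves nothing. The documents do not support that. Sample Size expects attrition, the analysis uses complete cases, and Table 2 describes the endline as covering all women in the study Union Councils, so case mix may shift between waves. Main effects correct that, as the counter-case shows.

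A reader might also infer that the article offers adjustment as a guarantee of parallel trends. It does not: it speaks of potential confounding and states parallel trends separately as an assumption. Nor is adjustment the only source of comparability. All eight Union Councils lie in one Taluka, were chosen as severely flood-affected, and have the same types of facility.

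Most of the sensible covariate list is already named regardless of imbalance; only the additional factors depend on observed imbalance. That an endline trauma value, possibly affected by the intervention, would enter the model is a possibility left open, not something the article says.

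**Conclusion.** The point holds in a limited form. On the natural reading, the adjusted DID does not address different trends caused by an imbalanced baseline factor whose effect changes over time. Under the assumed 20 to 30 point imbalance and a log-odds change of 0.5 to 0.7, the null odds ratio is about 1.10 to 1.23 with or without main effects, roughly a third to 70% of the planned log odds ratio; the smallest inputs tried give about a tenth. If no imbalanced factor modifies the trend, there is no bias.

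It would be wrong to conclude that the trial's estimate is biased, or that half or more of the effect would be hidden. Every bias size rests on assumed covariate inputs, and neither their size nor their direction can be read from the article. Effectiveness is the secondary objective; the primary feasibility proportions are unaffected. The change is still worth making, because it is cheap and gives a better method on data the trial already plans to collect.

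**What to change.** - Enter the baseline values of the covariates already named (age, education, marital status, parity, socioeconomic status, flood trauma), each with its covariate-by-time interaction, whether or not they look imbalanced. Alternatively, weight the control women to the intervention arm's baseline profile and then run the DID.
- State that only baseline trauma values are used.
- Limit the claim to confounding by measured baseline factors. Neither option protects against trends driven by unmeasured factors, so parallel trends remains an assumption, now conditional on those covariates.

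The cost is at least six extra model terms (more where a covariate has several categories) or one weighting step, with a small loss of precision that has not been quantified here. No new data are needed. In the simulations the added term kept the rejection rate near 5% when it was not needed (4.5%).
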